### **9.2.3 Sub-group analysis**

Subgroup analyses will be limited to the same variables which were used as minimisation variables (see Section 5.6.1). Tests for statistical heterogeneity (e.g. by including treatment group by subgroup interaction parameter in the linear regression model) will be performed prior to any examination of effect estimate within subgroups. Our hypothesis is that UPA may be more effective in older ( $>35$  years) and heavier ( $\text{BMI} > 25$ ) women and those who have a presence of fibroid or have experienced symptoms for longer than a year.

### **9.2.4 Handling missing data and other sensitivity analysis**

Every attempt will be used to collect full follow-up data on all women. In particular, the trial team will endeavour to follow-up participants even after protocol treatment violation. It is thus anticipated that missing data will be minimal. Patients with missing primary outcome data will not be included in the primary analysis. This presents a risk of bias. Thus, secondary sensitivity analyses will be performed to investigate the impact of any missing data for the primary, as well as any important secondary outcome. This will include worst (for those randomly missing) and best case assumptions (for those not able to complete the primary outcome as they no longer can have menstrual bleeding, i.e. because they have had a hysterectomy). We will also simulate missing responses using a multiple imputation approach. To explore the sensitivity of the primary MMAS

analysis to any ceiling effects (i.e. a high proportion returning a maximum responses, i.e. no problems with bleeding), a Tobit regression model will also be implemented.

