Where possible, the site and study team will aim to document the reason for withdrawing from the trial. Clear distinction will be made in the withdrawal/change of status form as to whether a participant is withdrawing from trial treatments whilst allowing further follow-up, or whether the participant refuses any follow-up. If a participant explicitly withdraws consent to have any further data recorded their decision will be respected and recorded. All communication surrounding the withdrawal or change of status will be noted in the patient's hospital records and in the trial database and no further data will be collected for that participant. For patients changing treatment but happy to allow further follow-up, the end of study ultrasound and bloods should be collected at the original intended time-point (weeks 49-57).

The target sample size of 220 patients includes a 20% loss to follow-up rate. Rates will be monitored to detect differential drop-out, which can bias clinical trial results and reduce the power of the trial to detect important differences.

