## **9 STATISTICS AND DATA ANALYSIS**

### **9.1 SAMPLE SIZE CALCULATION**

#### **9.1.1 RCT**

The trial has been designed to be able to detect a clinically useful difference in MMAS score between the two groups at twelve months with high power. The ECLIPSE Trial, which evaluated the effectiveness of LNG-IUS against Standard treatment for HMB (21) using MMAS as the primary outcome, demonstrated a difference of 13 points between the groups with a standard deviation of 24 points. This difference considered to be clinically meaningful (22) and is equivalent to approximately 0.5 standard deviations. To detect a difference of this size with 90% power ( $p=0.05$ ) would require 86 women in each group (172 in total). To allow for a 20% loss to follow-up or pregnancy, the sample size has been inflated to 220 women in total.

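### Read naturally, the worst-score rule in Protocol 9.2.4 imputes the same extreme MMAS value in both arms, so it cannot test departures in one arm only

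*Protocol*

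**What the plan says.** Protocol 9.2.4 makes the primary analysis a complete-case one: "Patients with missing primary outcome data will not be included in the primary analysis". It accepts that this risks bias, and so "secondary sensitivity analyses will be performed to investigate the impact of any missing data for the primary" and for important secondary outcomes. Two approaches are named.

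- An extreme-value approach: "This will include worst (for those randomly missing) and best case assumptions". The best-case half is meant "for those not able to complete the primary outcome as they no longer can have menstrual bleeding", with hysterectomy as the example.
- Imputation: "We will also simulate missing responses using a multiple imputation approach".

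The extreme value is therefore chosen by reason for missingness. Neither treatment arm is mentioned, and no scenario with opposite values in the two arms is described.

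On the amount of missing data the protocol speaks twice. Section 9.2.4 says "It is thus anticipated that missing data will be minimal". Section 9.1.1 plans for more: "To allow for a 20% loss to follow-up or pregnancy, the sample size has been inflated to 220 women in total". Section 5.6.5 also recognises that loss may differ between arms: "Rates will be monitored to detect differential drop-out, which can bias clinical trial results".

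**The concern.** A sensitivity analysis for missing data should show how far the missing scores would have to differ from the observed ones before the conclusion changes. What threatens a treatment comparison is mainly a departure that differs between the arms. Giving the same extreme value to missing women in both arms does not vary that quantity. Two other things happen instead.

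- With equal loss, the difference shrinks by the missing fraction, and the cluster of scores at the end of the scale inflates the SD.
- With unequal loss, the gap in response rates is turned into MMAS points, whatever the treatments do.

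Multiple imputation as usually run assumes that scores are missing at random. The worst/best rule is then the only named check on departures from that assumption. If it cannot test departures in one arm, the trial has no named analysis that does.

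**Working it through.** **Inputs from the Protocol.** MMAS runs from 0 (not affected) to 100 (worst affected) (2.2.1). Target difference 13 points, SD 24, 90% power, 86 per group, 220 in total with 20% loss (9.1.1). Equal allocation (5.6.2), hence 110 per arm. Two-sided tests (9.2).

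**Assumptions not in the Protocol.** It gives no 12-month mean, so an LNG-IUS mean of 30 to 50 is assumed. Scores are treated as normal and missing completely at random, and the comparison is unadjusted. The 25%/15% split is illustrative and averages the planned 20%.

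**The plan's own figure.** For 0.5 SD, two-sided 5%, 90% power:
- normal approximation: n = 2 × (1.960 + 1.282)² / 0.5² = 84.1, so 85 per group; the exact t calculation gives 86, as stated;
- 172 / 0.8 = 215, against 220 stated.

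The unrounded 13/24 = 0.54 SD would need 73 per group, so the rounded 0.5 was used. That is why complete-case power at SD 24 exceeds 90%: with 88 per arm, SE = 24 × √(2/88) = 3.62, 13/3.62 = 3.59, power about 95%.

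**Effect of the rule.** Let a fraction m of an arm with mean μ be set to 100. Then:
- arm mean = (1 − m)μ + 100m
- arm variance = (1 − m) × 24² + m(1 − m)(100 − μ)²
- SE of the difference = √[(V_UPA + V_LNG)/110]

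Differences are UPA minus LNG-IUS; negative favours UPA.

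*Example: LNG-IUS mean 30, UPA mean 17, 20% missing in each arm.*
- LNG-IUS: 0.8 × 30 + 20 = 44.0; variance 0.8 × 576 + 0.16 × 70² = 1,244.8 (SD 35.3)
- UPA: 0.8 × 17 + 20 = 33.6; variance 0.8 × 576 + 0.16 × 83² = 1,563.0 (SD 39.5)
- Difference −10.4, SE √(2,807.8/110) = 5.05, power about 54%

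| Scenario | Mean 30 | Mean 40 | Mean 50 |
|---|---|---|---|
| True −13, 20% / 20% missing | −10.4, power 54% | −10.4, power 61% | −10.4, power 69% |
| True 0, 20% / 20% | 0.0, rejects 5% | 0.0, rejects 5% | 0.0, rejects 5% |
| True 0, 25% UPA / 15% LNG-IUS | +7.0, rejects 32% | +6.0, rejects 28% | +5.0, rejects 25% |
| True −13, 25% UPA / 15% LNG-IUS | −2.8, power 8% | −3.8, power 13% | −4.8, power 20% |

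The third row is (0.25 − 0.15) × (100 − μ). Its sign reverses if LNG-IUS loses more. SD 26 gives similar results.

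**Smaller loss.** At 5% in each arm, 13 becomes 12.35 and power is 89-93%. At 15% against 5% with no true effect, rejection is still 28-39%.

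**Comparison with arm-opposed values.** With 20% missing per arm and a complete-case difference of −13:
- missing UPA = 0, missing LNG-IUS = 100: 0.8 × (−13) − 20 = −30.4
- the reverse: 0.8 × (−13) + 20 = +9.6
- 100 in both arms: −10.4

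The common value gives one point inside that range, at neither end.

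**The case against.** The strongest reply is that Protocol 9.2.4 states no such rule. It names neither an arm nor a numerical score, its list is not exhaustive, and 9.2 defers detail to a full statistical analysis plan. Imputed values and scenarios by arm are ordinary content for that plan. This stands in part: imputing the same value in both arms is a reading. It is the natural one, because the value is tied to the reason for missingness and the hysterectomy half is plainly the same in both arms.

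A reader might also infer several stronger things, which the documents do not support.

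- *That the protocol offers the rule as a bound on the treatment effect.* It says only that the analyses investigate the impact of missing data.
- *That the worst score contradicts an assumption of missing at random.* The wording may simply mean missing without a structural reason, in contrast to women who no longer menstruate.
- *That the check would usually contradict a true positive.* At equal 20% loss and means of 30-50 it agrees in 54-69% of trials. Only at the assumed unequal split does agreement fall to 8-20%.
- *That it creates false effects in general.* With equal loss and no true effect it gives 0.0 and 5% rejection.

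The sizes also rest on assumed means and splits, a normal model for a bounded scale, and an unadjusted test where 9.2.1 specifies covariate adjustment. Differential loss is to be monitored, and any odd result would be read beside the complete-case and imputed analyses. All of this limits the weight of the point. None of it gives the rule the ability to examine one arm at a time.

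**Conclusion.** The point holds as a weakness in one secondary sensitivity analysis, on the natural reading of 9.2.4. As worded, the worst-score assumption does not test departures confined to one arm. At the planned 20% loss in each arm it turns 13 points into 10.4 and lowers power from about 95% to about 54-69%. At an assumed 25% against 15% with no true effect it produces 5-7 points, significant in about 25-32% of trials.

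These figures assume SD 24, an LNG-IUS mean of 30-50 and loss unrelated to outcome. The loss split is illustrative, and the documents do not say that loss will differ between arms. If missing data are as few as 9.2.4 expects and are balanced, the distortion is small. The primary analysis is not affected, and multiple imputation is already planned.

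**What to change.** Replace the common worst-score assumption with delta-adjusted (tipping-point) imputation:

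1. Take the planned multiple imputation as the base, with treatment arm, minimisation variables, and baseline, 3- and 6-month MMAS in the imputation model.
2. Add a delta to imputed 12-month scores in UPA only, then in LNG-IUS only, in pre-specified steps, for example from 0 to 26 points worse (twice the target difference).
3. Report the delta at which the conclusion changes, or that none within the scale does so. A delta applied to a fraction m of one arm moves the difference by m × delta, so at 20% missing a delta of 26 moves it 5.2 points. The range may need to extend further.

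At the least, say that worst and best values will be applied in opposite directions by arm, both ways round, and state which end of the scale is worst. Section 2.2.1 makes 100 the worst score, while the ceiling-effect sentence in 9.2.4 treats the maximum response as the absence of a problem.

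The cost is a change of analysis wording, a pre-specified delta range and a few extra runs of an imputation already planned. No new data are needed. Priority is low to moderate.

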#### 9.2.5 Timing of assessments

An interim report including the analysis of major endpoints will be provided in strict confidence to a Data Monitoring Committee at intervals of at least 12 months, or as to a timetable agreed by the DMC prior to study commencement (see Section 11.4 for further details on trial data monitoring including the use of pragmatic stopping criteria). Final analysis will be performed once all women have completed twelve months follow-up.

### 9.3 PROPOSED ANALYSES – MECHANISTIC STUDY

Outcomes for the n=20 prospectively studied women biopsied at 6 and 12 months will be compared to each participant's own baseline biopsy as a control. Outcomes (e.g. PH3 immunoscore changes within groups over time) will be analysed using paired t-tests following an appropriate transformation and also by using non-parametric methods (e.g. Wilcoxon signed rank test) for confirmation.

## 10 ADVERSE EVENTS AND PHARMACOVIGILANCE

The Investigator is responsible for the detection and documentation of events meeting the criteria and definitions detailed below. These tasks may also be delegated to a qualified member(s) of the research team. Assessment of events may be delegated to other suitably qualified physicians in the research team who are trained in recording and reporting adverse events.

Participants will be instructed to contact their investigator at any time after randomisation if any symptoms develop. In the case of an AE, the Investigator should initiate the appropriate treatment according to their medical judgment.

### 10.1 DEFINITIONS

An **adverse event** (AE) is any untoward medical occurrence in a clinical trial participant which does not necessarily have a causal relationship with an investigational medicinal product (IMP).

An **adverse reaction** (AR) is any untoward and unintended response to an IMP which is related to any dose administered to that participant.

A **serious adverse event** (SAE), **serious adverse reaction** (SAR). Any AE or AR that at any dose:

- results in death of the clinical trial participant;
- is life threatening\*;

- requires in-patient hospitalisation^ or prolongation of existing hospitalisation;
- results in persistent or significant disability or incapacity;
- consists of a congenital anomaly or birth defect;
- results in any other significant medical event not meeting the criteria above.

\*Life-threatening in the definition of an SAE or SAR refers to an event where the participant was at risk of death at the time of the event. It does not refer to an event which hypothetically might have caused death if it were more severe.

^Any hospitalisation that was planned prior to randomisation will not meet SAE criteria.

**A suspected unexpected serious adverse reaction (SUSAR)** is any AR that is classified as serious and is suspected to be caused by either IMP, that it is not consistent with the information about the IMP in the Summary of Product Characteristics (SmPC).

## 10.2 IDENTIFYING AES AND SAES

There may be expected and unexpected adverse reactions, which may be minor or serious, associated with UPA and LNG-IUS when used in women affected by HMB. The adverse event profile for LNG-IUS is well defined, as the system has been licenced for over a decade, and hence the collection of expected adverse events is not required. For example, elective admission for LNG-IUS insertion or elective admission for hysterectomy would not need to be classified as a serious adverse event. The focus for safety reporting of UPA is on changes to the endometrium.

Open-ended and non-leading verbal questioning of the participant will be used to enquire about AE/SAE occurrence during each study visit and in postal questionnaires. Participants will also be asked if they have been admitted to hospital, had any gynaecological treatments, used any new medicines or changed concomitant medication regimens. If there is any doubt as to whether a clinical observation is an SAE, the event will be recorded and reported.

AEs and SAEs may also be identified via information from the endometrial biopsy, which will be recorded on the histopathology report form and SAE form if necessary. Untoward findings may incidentally be found in women in the mechanistic study, for example unexpected pelvic masses seen on by MR imaging. These will be reported to the local Principal Investigator who will assess whether they constitute an AE or SAE and the appropriate clinical management will be determined. If any untoward findings meet seriousness criteria they will be subject to onward reporting.

All diagnoses of endometrial cancer, ovarian cancer, cervical cancer, breast cancer or ductal carcinoma must be reported as a SAE.

### 10.3 RECORDING AES AND SAES

When an AE/SAE occurs, it is the responsibility of the Investigator to review all documentation (e.g. hospital notes, laboratory and diagnostic reports) related to the event. The investigator will then record all relevant information regarding SAEs on the SAE form (if the AE meets the criteria of serious) and record all unexpected AEs in both groups on the AE log. Expected AEs do not need to be recorded, unless they meet seriousness criteria, listed in the SmPC Reference Document.

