# 1 INTRODUCTION

## 1.1 BACKGROUND

Menstrual bleeding complaints affect quality of life and comprise a substantial societal burden, including major impact on health care use and costs. In the UK, 1 million women annually seek help for heavy menstrual bleeding (HMB; Clinical Guideline 44; <http://www.nice.org.uk/guidance/cg44>) and reported treatment costs exceed £65m; an estimated 3.5 million work-days are lost annually (7).

Current commonly prescribed medical treatments for HMB include COX-inhibitors, anti-fibrinolytic therapy, and the levonorgestrel-releasing intra-uterine system (LNG-IUS). NICE recommends LNG-IUS as the first line medical treatment. The LNG-IUS significantly reduces the burden of heavy menstrual bleed compared to non-hormonal treatments, substantially reduces menstrual blood loss, often resulting in amenorrhoea, but the unpredictable unscheduled bleeding may be problematic, with up to a third ceasing use within 2 years (8, 9).

A new group of pharmacological agents, called selective progesterone receptor modulators (SPRMs) are in development and have the potential to provide effective oral treatment for HMB. These SPRMs impart a tissue-specific partial progesterone antagonist effect, acting on progesterone receptors in both endometrial and underlying myometrial tissue. Ulipristal Acetate (UPA) is the only SPRM to have been licensed for use in clinical practice albeit restricted to two cycles of 3 month pre-treatment of fibroids prior to surgical removal. The introduction of this drug followed evaluation in two concurrent randomised controlled trials (RCTs) (10); 'PEARL I' assessed the efficacy of UPA 5mg and 10 mg daily on uterine bleeding and fibroid volume against placebo and 'PEARL II' assessed the efficacy and side effects of UPA versus the gonadotrophin-releasing hormone analogue (GnRHa) leuprolide acetate for treating symptomatic uterine fibroids prior to surgery (10). Both trials demonstrated control of HMB in over 90% of women and amenorrhoea in over 70% women. Control of HMB was achieved significantly more quickly in the UPA group. There was a statistically significant reduction in uterine fibroid size (-21% in the 5mg and -12% in the 10mg groups). Compliance with treatment over 3 months was high in both studies (96% and 98%) and reported side-effects were limited to minor complaints, of which headache (4%) and breast complaints (4%) were the most common, with no difference between active drug and placebo.

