#### **2.1.2 Secondary Objectives**

- Ascertain whether UPA use beyond 3 months and up to 12 months duration is associated with histological changes to the endometrium, and if so, whether this compromises safety.

- Ascertain whether UPA is more effective than LNG-IUS in relation to menstrual blood loss, sexual activity, generic quality of life, satisfaction with treatment, patient reported adverse events, and compliance at 3, 6 and 12 months.
- Determine the response to UPA and LNG-IUS treatment difference in the presence of uterine fibroids in terms of (i) alleviation of HMB and (ii) change in uterine/fibroid volume.

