#### 6.4.2 Monitoring compliance

Follow-up questionnaires will ask for self-reported compliance to the allocated treatment. We may also collect data on adherence via a text message at various time points. LNG-IUS drug compliance will be participants who have had the coil fitted within 5 weeks post-randomisation.

UPA compliance will be those participants who report in the follow-up questionnaire to have taken the drug for at least 5 days per week. UPA drug compliance may also be evaluated by 'pill-counting'.

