#### 10.4.3 Assessment of Expectedness

If an event is judged to be an AR, the evaluation of expectedness will be made based on knowledge of the reaction and the relevant product information documented in the SmPC which is stored in the site file and pharmacy file.

The event may be classed as either:

**Expected:** the AR is consistent with the toxicity of the IMP listed in the SmPC.

**Unexpected:** the AR is not consistent with the toxicity in the SmPC.

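### LNG-IUS compliance is fixed once the coil is fitted, and expected non-serious adverse events need not be recorded, so two between-arm comparisons in the secondary objective (2.1.2) cannot be made on equal terms as written

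*Protocol*

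**What the plan says.** **Objective.** Section 2.1.2 sets out to show whether UPA is more effective than LNG-IUS on several measures, ending with "patient reported adverse events, and compliance at 3, 6 and 12 months".

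**Compliance.** Section 6.4.2 gives each arm its own rule. For the coil: "LNG-IUS drug compliance will be participants who have had the coil fitted within 5 weeks post-randomisation". For UPA, a woman is compliant if she reports in the follow-up questionnaire that she took the drug on at least 5 days a week. Section 1.1 says of LNG-IUS that unscheduled bleeding may be a problem, "with up to a third ceasing use within 2 years".

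**Adverse events.** Section 10.3 tells the investigator to "record all unexpected AEs in both groups on the AE log", and then adds: "Expected AEs do not need to be recorded, unless they meet seriousness criteria, listed in the SmPC Reference Document". Section 10.4.3 classes a reaction as expected when "the AR is consistent with the toxicity of the IMP listed in the SmPC", and 10.4.2 refers to the SmPC relevant to the product. Section 10.2 justifies the omission by the well-defined LNG-IUS profile, "hence the collection of expected adverse events is not required", but 10.3 applies it to both groups.

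**Timing.** Section 8.1.1 asks about adherence, discontinuation and serious adverse events at all three follow-ups. Table 1 has one row for compliance, adverse events and three other patient-reported items, marked at 12 months only.

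**The concern.** A comparison of compliance over time needs a measure that can change over time in both arms. The LNG-IUS rule records a single early event, while the UPA rule is applied afresh at each questionnaire. A woman whose coil comes out in month 2 is still compliant at 3, 6 and 12 months. A woman who stops UPA in month 2 is not. The gap widens with follow-up and comes from the definition, not from the women's behaviour.

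For adverse events, the wording of 10.3 is the same in both arms but what it filters out need not be. If expectedness is read from each product's own label, a non-serious complaint listed for one product only may go unrecorded in that arm and be logged in the other. An analysis plan cannot recover events that were never recorded, so this has to be settled in the protocol. The primary outcome is not affected.

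**Working it through.** The protocol states no figure on this point that could be reproduced. The first part compares rules and sizes the effect under assumptions; the rest is a reading of the text.

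**1. Compliance: the two rules side by side**

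| Woman's course | Class under 6.4.2 at 12 months |
|---|---|
| LNG-IUS, fitted in week 2, still in situ | compliant |
| LNG-IUS, fitted in week 2, removed or expelled in month 2 | compliant |
| UPA, still reporting at least 5 days a week | compliant |
| UPA, stopped in month 2 | not compliant |

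**2. Compliance: size**

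Inputs:
- Cessation of LNG-IUS within 24 months, *c*. The protocol gives up to one third (section 1.1). The lower values of 10% and 20% are assumptions.
- Constant hazard (assumption).
- All coils fitted within 5 weeks (assumption).
- 110 women per arm: the 220 of section 9.1.1 divided by 2 for equal allocation (5.6.2). This is the planned number; recruitment is suspended.

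Proportion stopped by month *t*: p(t) = 1 − (1 − c)^(t/24). For example, at 12 months with c = 1/3: 1 − (2/3)^0.5 = 0.184, and 0.184 × 110 ≈ 20 women.

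| Stopped by 24 months | 3 months | 6 months | 12 months |
|---|---|---|---|
| 10% (assumed) | 1.3% (1.4 of 110) | 2.6% (2.9) | 5.1% (5.6) |
| 20% (assumed) | 2.8% (3.0) | 5.4% (6.0) | 10.6% (11.6) |
| One third (protocol's upper figure) | 4.9% (5.4) | 9.6% (10.6) | 18.4% (20.2) |

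These are the women classed as compliant although the coil is out. If fewer coils are fitted on time, each entry shrinks in proportion. If stopping is concentrated in the first year, the 12-month figures rise; with c = 1/3 they cannot exceed one third.

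**3. Adverse events**

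- Section 10.3: a non-serious event is logged if unexpected; if expected, it need not be.
- Sections 10.4.2 and 10.4.3: expectedness refers to the SmPC of the product concerned. That this means the woman's allocated product is an inference, since 10.3 does not say so.
- Section 8.1.1: the questionnaire item covers serious adverse events, so it does not restore the missing non-serious ones.
- Section 2.2.2: the listed safety outcome is mainly serious and unexpected events, which is narrower than objective 2.1.2.

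One event shows the scale. Section 6.6.3 puts hot flushes on UPA at 12.7% on average, with 1.0% and 24% in the two trials it cites. If they count as expected for UPA, 0.127 × 110 ≈ 14 women (1 to 26 over that range) would have an event that need not be recorded. Whether it would be logged in the LNG-IUS arm depends on a label that the protocol does not reproduce. The direction of any distortion is therefore unknown.

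**4. Timing**

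Sections 2.1.2 and 8.1.1 name three follow-ups; Table 1 marks compliance and adverse events at 12 months only. The protocol contradicts itself here.

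**The case against.** The strongest reply on compliance is that the information is not lost. Section 6.4.2 itself begins with self-reported compliance in the follow-up questionnaires. Section 8.1.1 collects LNG-IUS adherence and discontinuation at every follow-up, 2.2.2 lists participant-reported adherence and reasons for changing treatment as an outcome, and 5.6.5 records changes of treatment on a status form. The analysis is by intention to treat, and no analysis in section 9.2 uses the 5-week rule. All of this stands. The fault lies in the definition, not in the data collection, and that is why the repair is cheap. It does not make the definition usable for the comparison in 2.1.2.

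On adverse events, the reply is that 10.2 and 10.3 are safety-reporting rules that fit the narrower outcome in 2.2.2, and that 10.3 permits omission without requiring it. Bleeding, pelvic pain, sexual functioning and satisfaction are in any case measured in the same way in both arms. This also largely stands. What remains is that the objective promises more than the recording rule can deliver.

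A reader might go further and infer a demonstrated bias. An event with a true rate of 10% in both arms, listed for one product only, would appear as 11 of 110 against 0 of 110 (Fisher exact p = 0.00075). The documents do not support that: the figure assumes complete suppression in one arm and full follow-up of the planned numbers, and no SmPC list is shown. Nor do they support inferring that this comparison would decide which treatment is used.

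**Conclusion.** The compliance point holds. As written, 6.4.2 misclassifies women whose coil is removed or expelled after timely fitting, and the comparison in 2.1.2 then favours LNG-IUS by about 5 to 18 percentage points at 12 months (about 6 to 20 of 110 women). That size rests on 10% to one third stopping within 2 years, a constant hazard and timely fitting throughout; only the upper figure comes from the protocol. It would be too strong to say that falling LNG-IUS use goes unseen, because 8.1.1 captures it.

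The adverse event point holds in a limited form. Section 10.3 cannot support a between-arm comparison of patient-reported non-serious events, and the recorded set may differ by arm in a direction that the protocol does not reveal. The contradiction over timing in Table 1 is plain. These are secondary objectives and should be corrected; the primary analysis is unaffected.

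**What to change.** - **Section 6.4.2.** Define LNG-IUS compliance at each time point as fitted within 5 weeks of randomisation and still in situ at that assessment, using the adherence and discontinuation items in 8.1.1. Report UPA stops caused by the Urgent Safety Measure as a separate category, so that they are not counted as the woman's non-compliance.
- **Section 2.1.2.** Restrict the adverse event comparison to serious adverse events. Section 10.3 has these recorded in both arms whether or not expected, and they are the main focus of the outcome in 2.2.2. Present the non-serious adverse event logs descriptively by arm, without a between-arm test. Recording every non-serious event from now on is less attractive: recruitment is suspended, earlier events may not be recoverable, and two recording rules would be mixed in one trial.
- **Table 1.** Show compliance and adverse events at 3, 6 and 12 months, as in 2.1.2 and 8.1.1. The row also carries satisfaction, rating and recommendation, so it is better split than ticked across.

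The cost is slightly more derivation work and a narrower adverse event objective. No new data item is needed and no clinical rule changes.
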